## Abstract

**Background:**

Most people do not engage in sufficient physical activity to confer health benefits and to reduce risk of chronic disease. Healthcare professionals frequently provide guidance on physical activity, but often do not meet guideline levels of physical activity themselves. The main objective of this study is to develop and test the efficacy of a tailored intervention to increase healthcare professionals’ physical activity participation and quality of life, and to reduce work-related stress and absenteeism. This is the first study to compare the additive effects of three forms of a tailored intervention using different techniques from behavioural theory, which differ according to their focus on motivational, self-regulatory and/or habitual processes.

**Methods/Design:**

Healthcare professionals (*N* = 192) will be recruited from four hospitals in Perth, Western Australia, via email lists, leaflets, and posters to participate in the four group randomised controlled trial. Participants will be randomised to one of four conditions: (1) education only (non-tailored information only), (2) education plus intervention components to enhance motivation, (3) education plus components to enhance motivation and self-regulation, and (4) education plus components to enhance motivation, self-regulation and habit formation. All intervention groups will receive a computer-tailored intervention administered via a web-based platform and will receive supporting text-messages containing tailored information, prompts and feedback relevant to each condition. All outcomes will be assessed at baseline, and at 3-month follow-up. The primary outcome assessed in this study is physical activity measured using activity monitors. Secondary outcomes include: quality of life, stress, anxiety, sleep, and absenteeism. Website engagement, retention, preferences and intervention fidelity will also be evaluated as well as potential mediators and moderators of intervention effect.

**Discussion:**

This is the first study to examine a tailored, technology-supported intervention aiming to increase physical activity in healthcare professionals. The study will evaluate whether including additional theory-based behaviour change techniques aimed at promoting motivation, self-regulation and habit will lead to increased physical activity participation relative to information alone. The online platform developed in this study has potential to deliver efficient, scalable and personally-relevant intervention that can be translated to other occupational settings.

**Trial registration:**

Australian New-Zealand Clinical Trial Registry: ACTRN12616000462482, submitted 29/03/2016, prospectively registered 8/04/2016.

## Background

Physical inactivity is related to increased risk of a number of chronic diseases (e.g., cardiovascular disease, Type 2 diabetes, certain types of cancer, obesity) [1, 2]. Engaging in regular physical activity is related to reduced risk of chronic diseases [2]. In addition, positive outcomes of physical activity include improved quality of life, better sleep, and reduced stress [3, 4]. World Health Organisation physical activity guidelines for adults to gain health benefits is to undertake at least 150 min of moderate intensity physical activity per week (e.g., walking, cycling), or at least 75 min of vigorous intensity physical activity per week (e.g., running, playing football) [5]. Globally, 1 in 4 adults does not meet these recommendations [5].

Healthcare professionals have a key role to play in the promotion of physical activity [6]; however they often do not meet guideline levels of physical activity themselves. For instance a study focussing on nurses’ physical activity (*N* = 325) indicated that more than half of the assessed sample did not meet guideline levels of physical activity [7]. Those who were less active were also more likely to report poor general health and worse sleep patterns than their active counterparts. Despite significant health education among health care professionals, it appears that the health knowledge often does not translate into their own health behaviours [7–9].

In addition, there is a relationship between personal physical activity behaviours of healthcare professionals and their health-promotion practice. A systematic review [10] of cross-sectional studies (*N* = 13) investigating this relationship found that a higher personal physical activity level in healthcare professionals was associated with higher physical activity-promoting practices in most studies. Health professionals with positive attitudes towards physical activity were also more likely to promote physical activity to their patients.

Healthcare professionals often exhibit unhealthy lifestyle behaviours with work-related stress identified as the most frequently-cited reason [11]. Professionals report that hospitals are a highly stressful work environment, and irregular shift work often places an additional strain on the hospital employees [12]. Sleep patterns and sleep quality among healthcare professionals were insufficient for good health [13] and physical activity is a recognised means to improve sleep quality [14]. In addition, nurses are prone to suffer lower back pain [15] and physical activity is recommended to this occupational group for managing back pain. As such, there is strong rationale for promoting physical activity among healthcare professionals.

The workplace is reported as a suitable environment for making changes in the physical activity and improving health of employees [16]. Increased participation in physical activity in healthcare professionals can be promoted using behavioural interventions which utilise persuasive strategies and techniques to encourage individuals to change their behaviour (e.g., goal setting, planning, providing social support) [17, 18]. Such interventions have been shown to be effective in promoting increased uptake and maintenance of physical activity, including in the workplace [19–21], hence they may be suitable for promoting physical activity to healthcare professionals.

Other than identifying the importance of context in the delivery of interventions, such as the occupational setting for healthcare workers, it is also important to look at the means by which interventions may be delivered to employees in this context [22]. Recently computer-tailoring has been used to deliver behavioural interventions in health contexts and it has received increased attention as a means to effectively deliver personalised interventions to a wide audience at a relatively low cost [23]. These interventions provide users with individualised feedback based on their demographic profile and preferences. Users are prompted to provide information salient to the intervention (using an online questionnaire) and are subsequently provided with tailored feedback including information on behaviour change matched to their requirements and consistent with their responses. Pre-defined algorithms generate tailored content for the user based on user-provided information and the relevant behaviour change content that is stored in a database including all possible response options [24].

Web-based interventions have a number of advantages over face-to-face interventions: they have wide reach, comparatively low cost of implementation and delivery, and flexibility of intervention use at times and location convenient for the user [25, 26]. Tailoring web-based interventions also carries distinct advantages over non-tailored approaches: participants are presented only with relevant and personalised information, and non-relevant information can be omitted. This in turn may increase engagement and persuasion [27, 28]. In computer-tailored interventions, less information is presented to the users and more attention is directed to the relevant intervention content. In addition, consistent with the elaboration likelihood model of persuasion [29], information in the intervention is more likely to be thoughtfully attended to when it is personally relevant and when readers are motivated. Therefore, tailored interventions are more likely to be attended to and should lead to longer lasting behavioural change.

In addition to computer tailoring, there is also a growing literature supporting the use of short message service (SMS) or ‘text’ messaging to promote health behaviour. Research has demonstrated that delivering health behaviour messages via text messaging can promote health behaviour change in numerous contexts, including physical activity [30]. Text messaging has also been used in conjunction with web-based interventions to improve health behaviour and to enhance their effectiveness. A systematic review reported that the effectiveness of web-based interventions can be enhanced by the inclusion of SMS as a means to remind participants of intervention content or to augment it [31]. Therefore, adoption of web-based tailored interventions to promote physical activity augmented with text messaging, may be a useful, cost-effective means to promote physical activity to healthcare professionals.

In the context of physical activity promotion, computer-tailored behavioural interventions have been reported as effective [26, 32]; however further investigation of the mechanisms is needed in terms of evaluating these interventions and their effectiveness across multiple contexts. Investigating the mechanisms that can improve the effectiveness of computer-tailored interventions is crucial. Therefore, studies that isolate specific behaviour change techniques (BCTs) within intervention conditions using factorial designs will provide robust evidence for testing the impact of specific BCTs [18]. This means that knowledge of the specific individual components that are most likely to change behaviour will be identified.

### Theories of behaviour change and maintenance

Health behaviour change interventions are usually underpinned by psychological theories of behaviour change and maintenance. Many such theories have focused on *motivation* and intentions to explain and change behaviour (e.g., the Theory of Planned Behaviour) [33]. These theories view lack of engagement in health behaviours (e.g., physical activity) as primarily a problem with motivation, such that increasing motivation will directly lead to increases in behavioural participation. The theories also assume that motivation is a function of an individuals’ explicit, consciously-held beliefs about the behaviour [33]. However, theories of *volition* [34] indicate that motivation is a necessary but insufficient condition for behavioural enactment and suggests that volitional strategies (e.g., planning) that operate in a post-decisional manner (i.e. after intentions have been formed) lead to the effective execution of intentions into action because they enable an individual to more effectively recall their intended behaviour via prompts or cues that have been linked to the desired behaviour [35].

Dual process theories offer a broader perspective that integrates *motivational* and *volitional* processes, but also recognises that behaviour may also be influenced by more implicit, non-conscious processes [36–39]. Dual process theories propose that health behaviours are enacted through two processes – the conscious, deliberative processes such as those described in motivational and volitional theories, as well as non-conscious processes that occur automatically, outside an individual’s deliberation. The implicit processes reflect initiating or engaging in actions with very little deliberative, reasoned, and conscious decision making processes outlined in traditional motivational theories. Behaviours that may initially be controlled through deliberative, motivational pathways behaviours can, through a *habit-formation process* become controlled by automatic processes [40]. Habit formation likely occurs through learning of context-behaviour associations via context-dependent repetition of the behaviour usually in the presence of some rewarding contingency [41]. In some cases, the behaviour is enacted because repetition and experience has led the behaviour to occur without the need for any conscious control, as such the behaviour is classed as ‘habitual’ [42, 43].

Researchers applying these theories to predict and change behaviour have identified strategies and techniques to promote the development of habits [40]. These techniques should be separable and able to be isolated from techniques that promote, for example, increased behavioural engagement via the motivational and volitional pathways identified in dual process theories. As a consequence, factorial-type designs should be able to demonstrate the unique effects of techniques related to motivation and volition and techniques related to habit promotion on health behavior change. Such designs may also permit demonstration of whether the addition of components targeting specific processes (e.g., motivational, volitional, habitual) may lead to incremental changes in behaviour relative to each set of techniques alone.

### The present study

There is a need for cost-effective, efficacious behavioural interventions to increase physical activity in healthcare professionals [13]. Research has suggested that theory-based interventions adopting multiple BCTs are effective in increasing physical activity behaviour [31]. Recent research efforts have focused on linking BCTs with underlying theoretical mechanisms of action [44]. However, few studies have systematically examined the efficacy of specific groups of BCTs that are thought to operate through one of the three specified processes (motivational, volitional, and habit-forming) and assessed their independent and additive effects on behaviour change. The purpose of the current study, the Physical Activity Tailored intervention in Hospital Staff (*PATHS*) study, is to evaluate the efficacy of a computer-tailored intervention to increase physical activity and quality of life, and decrease work-related stress and absenteeism, in hospital healthcare workers. The intervention will examine the additive effects of groups of BCTs derived from theories of motivation, volition, and habit on physical activity behavior change. The research is unique as it will provide the first evidence of the efficacy of techniques derived from these three theoretical approaches applied in a workplace context. The study will adopt a randomised controlled design to test and compare the effects of three distinct groups of BCTs derived from theory and focusing different processes of behaviour changes on study outcomes: motivation, self-regulation, and habit formation.

Specifically, the intervention will include motivational techniques to increase motivation and self-efficacy to engage in physical activity, self-regulatory techniques to increase capability and skills to initiate and regulate behaviour change, and habit-based techniques to increase the automatic, non-conscious tendencies to engage in physical activity on presentation of contextual and time-relevant cues. Three intervention conditions are proposed, each defined by the sets of BCTs in an additive design: (1) motivational BCTs; (2) motivational plus self-regulatory BCTs; and (3) motivational plus self-regulatory and habit formation BCTs. The intervention groups will be compared to a control condition that will receive basic non-tailored information about physical activity.

## Methods

### Participants

Full- and part-time hospital staff including midwives, clinical nurse managers, clinical nurses, registered nurses, enrolled nurses, and patient care assistants will be eligible to participate in the *PATHS* study. Participants will be recruited from hospitals in Perth, Western Australia. Staff working in shift and non-shift patterns will be eligible to participate. No restrictions will be placed on the type of contract and number of hours worked. Participants are eligible if they fail to meet the recommended weekly level of 150 min of moderate intensity physical activity because the intervention is designed for people who fail to meet this level.

Individuals who self-report a physical condition or impairment preventing them from being physically active will be excluded from the study. They will be screened using the Physical Activity Readiness Questionnaire (PAR-Q) prior to study consent [45]. However, individuals who are not eligible to participate in the study based on PAR-Q measures can still consult their GP to obtain approval. Hospital employees who do not have a mobile phone that allows them to receive text messages, who do not have access to internet on their mobile phone, computer or tablet outside of work, who are already meeting weekly recommended levels of physical activity or are currently participating in another physical activity program (e.g., a structured weight loss program, regular meetings with personal trainer or coach) will be excluded.

### Recruitment

Participants will be recruited from different hospital wards via email messages and printed letters that will be sent to all potentially eligible employees, accompanied by a description of the study and its requirements and inviting them to take part. Study posters and leaflets advertising the study will be placed throughout hospital premises. Members of the *PATHS* team will also visit each ward to promote the study, alongside ward managers. The promotional materials will advertise the study as research investigating the development of a web-based tool to improve employees’ physical activity, wellbeing and health. Recruitment materials (including posters, leaflets, emails, and printed letters) will direct interested staff to the project website, which will provide study information and will allow them to assess eligibility and register to participate. A formal statement of consent will be signed in person at the first meeting with the study researcher.

### Study design

The *PATHS* study is a pragmatic four-group intervention trial adopting a randomised control design with assessments of primary and secondary outcomes at baseline and 3-month follow-up time points (see Fig. 1). We chose randomisation of individuals within hospitals (rather than randomisation of hospitals or wards) because individual randomisation was more efficient and more feasible with continuous recruitment of the participants; program was delivered to individuals rather than groups so contamination across intervention groups was not considered a major risk [46]. The project comprises three intervention conditions and a no intervention condition, in which participants receive information about the study only. This will serve as a control condition. Each condition includes a group of theory-based BCTs designed to test the additive effects of the specific BCT groups on study outcomes:
**Control condition** – provision of information about physical activity only
**Motivation condition** – provision of information + motivational BCTs
**Self-regulation condition** – provision of information + motivational BCTs + self-regulatory BCTs
**Habit condition** – provision of information + motivational BCTs + self-regulatory BCTs + habit formation BCTs

**Fig. 1 Fig1:**
[figure not shown]
CONSORT flow diagram [91]

### Procedure

After screening, eligible participants will be contacted by a study researcher who will arrange a one-on-one meeting (Figure 1, CONSORT flow diagram). During the meeting, the participant will receive a detailed explanation of the study, and its requirements and expectations from the researcher. They will also be provided with an information sheet providing the same information and outlining their rights to confidentiality and to withdraw from the study at any stage without consequence. Once the participant has had the opportunity to confirm their understanding of the project and have any questions answered, they will be asked to sign an informed consent form.

A study researcher will set up and initiate a GENEActiv activity monitor [47] for each participant, including programming the participant’s code number, date of birth, height, and handedness. Each monitor will be programmed to start collecting data from set up. Study participants will be required to wear the monitor on their non-dominant upper arm and will be provided with detailed instructions on how to wear the device. Participants will be instructed to wear it continuously throughout day and night for one week after the first meeting.

Eight days later, participants will meet with the researcher again to return the activity monitor. The study facilitator will check if sufficient data have been collected by the device (i.e., at least five days of wear with a minimum 16 h wear per day) [48]. If the participant fails to wear the activity monitor for the minimum time specified, they will be asked to wear it again for another seven days. At this second meeting, participants will also be asked to complete web-based baseline questionnaires using a provided tablet (Time 1).

After the second meeting, participants will be emailed a personalised login/password, and link to the website so they are able to login to the web-based *PATHS* study platform used to deliver the tailored intervention messages. Participants will be automatically randomly allocated online in an equal ratio to one of the four possible study conditions; a block randomisation will be used with block size of 16. If allocated to one of the three intervention conditions, they will be able to complete the first intervention session on the website immediately after completing the baseline assessments. If allocated to the control condition, they will receive an email directing them to the *Library* site for physical activity relevant information. The *Library* is a sub-section of the website with non-tailored evidence-based information about physical activity,

Across all conditions, participants will be encouraged to use and interact with the web-based *PATHS* platform for three consecutive months, completing sessions every fortnight. At the end of month three, participants will meet with the researcher and will be provided with a GENEActiv activity monitor to be worn for one week immediately post-intervention to assess physical activity. Participants will meet with the researcher again one week after they received the activity monitor to complete the post-intervention questionnaires and return the activity monitor (Time 2). All researchers collecting the data will be blinded to the allocation of participants’ study condition.

Following the three-month period, participants will be thanked for their study contribution via personal email and text message, and their names will be automatically entered into a prize draw allowing them to win shopping vouchers for their participation (four shopping vouchers, 20 AUD value per each hospital). Participants allocated to the control condition will then be given the opportunity to receive the content from one of the intervention conditions so that they are not prevented from participating in a potentially effective intervention. They will receive login details, password and link to the web-based tailored platform providing them with the option to engage in one of the three intervention conditions, chosen randomly. All study participants will be told that there are four different versions of the same program that differ in content and behaviour change techniques used. Participants will be asked not to share or compare intervention content to avoid study contamination among participants working on the same ward. They will be asked in the post intervention evaluation if they adhered to the aforementioned recommendation.

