#### Physical activity

The primary outcome will be measured physical activity over a one-week period prior to the intervention (Time 1) and for a further week immediately post-intervention at the three-month follow-up occasion (Time 2) using accelerometers (GENEActiv Ltd.) [47, 67]. Participants will be asked to wear the unit continuously for the seven day period on the non-dominant upper arm to comply with hospital hygiene regulations. The GENEActiv device is water proof and participants will be informed that they are free to choose whether to wear it while swimming, showering, or sleeping. Data will be collected at 60 Hz epoch frequency. Step counts will be derived from the acceleration data using open-source macros and they will be used as proxy for physical activity [47]. Participants will be supplied with a band specifically designed to fasten the monitor to the upper arm.

Secondary outcomes will be assessed at baseline (Time 1) and post-intervention (Time 2), and will include subjective measures of physical activity, sitting time, sleep, depression, anxiety, stress, quality of life, theory-derived correlates of physical activity and self-reported weight. Demographics, perceived neighbourhood environment, personal need for structure, internet self-efficacy, and planning skills/ability will be assessed at baseline (Time 1) only. Secondary outcomes assessed only at the post-intervention stage (Time 2) will include measures of intervention accessibility, usefulness and satisfaction with the intervention, as well as acceptability of the advice provided. Participants’ website usage (e.g., time spent on pages with specific intervention content, number of website visits) will be assessed throughout the study using Google Analytics.

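### The 16-hour valid-day rule conflicts with optional night wear, and nothing holds allocation back while a failed baseline monitor week is repeated

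*Protocol article*

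**What the plan says.** All references are to the protocol article.

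**Wear instruction.** Procedure: "Participants will be instructed to wear it continuously throughout day and night for one week after the first meeting". Physical activity (under Measures): "Participants will be asked to wear the unit continuously for the seven day period on the non-dominant upper arm", but the same paragraph adds that participants are "free to choose whether to wear it while swimming, showering, or sleeping". The Sleep section derives objective sleep only for those who choose night wear, and Table 3 marks that measure as optional at both time points.

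**Validity check.** Procedure: at the second meeting, eight days after the first, the record must show "at least five days of wear with a minimum 16 h wear per day". If it does not, "they will be asked to wear it again for another seven days".

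**What follows.** The baseline questionnaires (Time 1) are completed at that same second meeting. Procedure then continues: "After the second meeting, participants will be emailed a personalised login/password", and allocation is automatic and online. Participants in the three intervention conditions can do the first session straight after completing the baseline assessments. No sentence makes login or allocation depend on a valid monitor record, and no third baseline meeting is described.

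**Intended timing.** The Physical activity section places the baseline week of the primary outcome before the intervention. Step counts are the proxy for activity.

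**The concern.** There are two linked problems.

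First, staff are to ask for continuous wear, tell participants that night wear is their choice, and then apply a check that tolerates no more than 8 h off the body. The primary outcome is steps, so monitor time during sleep adds little to it. A record covering the whole waking day can still fail because the monitor was off overnight.

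Second, a failed check is what triggers the repeat week, and the text does not place that week before allocation. Table 2 shows session 1 giving feedback on current activity and a goal for the following two weeks, a period that would cover a repeat week running alongside it. Baseline activity is used three times in Study analysis: as one of the two time points in the condition-by-time model, as the control variable in the mediation models, and as the value carried forward for drop-outs. If the intervention raises steps, a baseline recorded under it understates that participant's change and distorts the baseline adjustment.

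**Working it through.** The plan states no figure on this point, so there is none to reproduce; its sample size does not depend on the wear rule.

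**1. What the 16 h rule tolerates**

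Inputs: at least 16 h per day on at least 5 days (Procedure); a seven-day wear period (Procedure and Physical activity). Let S be hours removed for sleep and O other hours removed.

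Wear = 24 − S − O. The day is valid if wear ≥ 16, that is, if S + O ≤ 8.

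| S (h) | O (h) | Wear (h) | Valid? |
|---|---|---|---|
| 7 | 0 | 17 | yes |
| 7 | 1 | 16 | yes, no slack |
| 7.5 | 1 | 15.5 | no |
| 8 | 0 | 16 | yes, no slack |
| 8 | 0.5 | 15.5 | no |
| 8.5 | 0 | 15.5 | no |

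**2. How often a nightly remover would fail the check**

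The documents give no distribution of off-body time. Assumption: total daily off-body time is normal with mean m and SD 1 h, and the seven days are independent.

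p = P(valid day) = Φ((8 − m)/1)

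P(pass) = Σ over k = 5 to 7 of C(7,k) p^k (1 − p)^(7 − k)

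Worked case, m = 8: p = Φ(0) = 0.5, so P(pass) = (21 + 7 + 1)/128 = 29/128 = 0.227.

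| m (h) | p | P(pass) | P(fail), rounded |
|---|---|---|---|
| 7 | 0.841 | 0.915 | 8% (0.0848 unrounded) |
| 7.5 | 0.691 | 0.628 | 37% |
| 8 | 0.500 | 0.227 | 77% |
| 8.5 | 0.309 | 0.033 | 97% |

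These rates apply only to people who remove the monitor every night. That share is unknown, so the table gives no trial-wide failure rate.

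**3. Order of events for someone who fails the check**

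| Step | Timing in the text | Conditional on valid wear? |
|---|---|---|
| Check of the first week's record | second meeting | – |
| Repeat wear, seven days | follows the failed check | – |
| Baseline questionnaires | second meeting | no |
| Login emailed | after the second meeting | no |
| Automatic allocation | described with the login | no |
| Session 1 (intervention conditions) | once the baseline assessments are complete | only if that term includes the monitor |
| Baseline activity week | before the intervention (Physical activity) | stated as intent; no step enforces it |

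Allocation during the repeat week is therefore not prevented. Session 1 before or during that week is possible only if the baseline assessments mean the questionnaires alone. If the term includes the monitor, session 1 waits but allocation still need not.

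**The case against.** The strongest reply is that this is an exception case in a condensed article and that the text already points the right way. The Physical activity section fixes the baseline week before the intervention. Session 1 opens only after the baseline assessments, and Table 3 lists the monitor among the Time 1 measures, so a natural reading includes it. This stands in part: the protocol does not plan to measure baseline under treatment. It leaves the order of the exception open, and for allocation there is no condition at all.

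It can also be said that both sections ask first for continuous wear, that participants receive detailed instructions, and that the Background describes sleep in this workforce as insufficient, so short removal times are plausible. This also stands: at a mean of 7 h off-body, about 92% of nightly removers pass.

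A reader might go further, in ways the documents do not support:

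- *Anyone who removes the monitor to sleep cannot record a valid day.* Exactly 8 h off still leaves 16 h, and 7 h of sleep leaves a margin.
- *Short-wear records are discarded from the analysis.* Procedure describes a check and a repeat wear; it does not give an exclusion rule for the analysis.
- *The same wearers will simply be missing at Time 2.* The article states no check or repeat wear at follow-up, but that silence may be filled by the full protocol or the analysis plan. Study analysis also provides multiple imputation for missing data other than drop-out.
- *Change is biased towards zero in the intervention arms.* That would concern only re-wearers who began session 1 before or during the repeat week, and their number cannot be derived.

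**Conclusion.** The point holds in a limited form. The wear instructions contradict each other on night wear, and the freedom to remove the monitor is in practical, not absolute, conflict with the 16 h rule. For people who remove it nightly, the chance of failing the check runs from about 8% to about 97% as mean off-body time goes from 7 to 8.5 h. This rests on the normal, SD 1 h and independent-days assumptions.

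The order of the repeat week, login and allocation is not fixed, so a repeated baseline can fall after allocation and, on one reading of the text, after session 1. That would breach the protocol's own intent for the primary outcome. Any bias is conditional on this happening and cannot be sized from the documents. No figure in the protocol changes. It is worth correcting because the remedy is cheap and protects the baseline of the primary outcome.

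**What to change.** 1. Reconcile Procedure with Physical activity, Sleep and Table 3 so that participants receive one wear instruction and the valid-day rule for steps matches it. One way is to judge validity for steps on waking wear and to keep 24-hour wear for the optional sleep measure. The sponsor should choose and justify the threshold, since the documents give no basis for a particular waking-hours figure.
2. State that login, allocation and session 1 are released only after valid baseline monitor data are confirmed or the single repeat week has ended, and that the baseline assessments include the monitor week.

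Cost: revised wording, a hold on the platform, and a delay of about one week for participants who repeat the wear. The sample size and the analysis model are unaffected.
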